### Primary outcomes

1. Difference in proportion of high risk individuals (with or without CVD) who are achieving optimal BP levels (systolic BP <140 mmHg) between the intervention and control periods.

### Secondary outcomes

1. Mean reduction in BP levels.

2. Change in other CVD risk factors, including body mass index; current smoking; reported healthy eating habits; and reported physical activity levels.

3. Self-reported use of BP and other cardiovascular medicines.

4. Quality of life (using the EQ-5D).

5. CVD events (using hospitalisation data).

### Statistical considerations

A total of 18 PHC clusters (with 3 villages per cluster) progressively randomised by a third to the intervention (Table 1) will provide >90% power (2α = 0.05) to detect an absolute difference of 6% in the proportion of people with optimal BP levels. This translates to an increase in the proportion achieving optimal BP levels from 39% (based on our previous data) to 45% and a mean systolic BP difference of around 3 mmHg. These calculations maximise the study power afforded by a stepped-wedge design and assume an intraclass correlation coefficient (ICC) of 0.03 (more conservative than the ICC of 0.01 previously observed in this population) and 5 time-points for data collection. The mean village population is approximately 4,000, with one-third aged ≥40 years. Based on previous data from the region, approximately 23% of adults aged ≥40 years (approximately 300 individuals per village) are likely to be classified as being at high risk, with around 35% of these having established CVD [9]. Considering a conservative participation rate at each survey, a PHC cluster size of 150 patients per time point (approximately 50 per village) is anticipated on the basis of the above calculation. Methods based on mixed effects models as described by Hussey and Hughes will be used to analyse intervention effectiveness on primary and secondary outcomes, accounting for outcome variable type, potential time effects, clustering and stepped wedge design [24].

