**Figure 2 F2:**
[figure not shown]
SMARTHealth study schema.

At baseline, a complete household survey (average of approximately 1,000 households per village) will be performed in each village. Trained field researchers will conduct interviews and make physical measurements using well-established methods [6]. In each household, every consenting adult aged ≥40 years of age will be assessed, and those at high risk of CVD will be identified, resulting in a census of all such individuals. Any individuals with extreme elevations of risk factors will be referred immediately for treatment. At each subsequent time point, data will be collected from a random independent sample of 15% of people identified at the baseline census as being at high risk (average of approximately 50 people per village). These data are for evaluation purposes only, and the ASHA and PHC doctors will not have access to this information.

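### The >90% power and the nominal type I error of a standard Hussey-Hughes analysis hold only if PHC effects do not drift over 24 months; the choice of ICC gives almost no protection against such drift

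*Protocol article*

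**What the plan says.** All of the following is in the protocol article.

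- **Analysis (Statistical considerations):** "Methods based on mixed effects models as described by Hussey and Hughes will be used to analyse intervention effectiveness on primary and secondary outcomes". The sentence goes on to say that outcome type, possible time effects, clustering and the stepped-wedge design will be accounted for. The random effects are not written out.
- **Power (same section):** the design "will provide >90% power (2α = 0.05) to detect an absolute difference of 6" percentage points, that is, "from 39% (based on our previous data) to 45" per cent.
- **Correlation (same section):** the calculations "assume an intraclass correlation coefficient (ICC) of 0.03 (more conservative than the ICC of 0.01 previously observed in this population"). Only one ICC is given. It is not split into within-survey and between-survey parts.
- **Size and timing:** 18 PHCs crossing over in three groups of six (Table 1), 150 people per PHC per survey, and "5 time-points for data collection". Each follow-up survey is a "random independent sample of 15% of people identified at the baseline census as being at high risk" (Data collection).
- **Secular change (Strengths and limitations):** the article accepts that regional change over time could bias the outcomes. Part of its answer is that the analysis adjusts for time.

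**The concern.** With a single constant intercept per PHC, two people in the same PHC are taken to be as alike 24 months apart as within one survey. In a stepped wedge the treatment effect is estimated largely from change within PHCs. A constant PHC effect therefore cancels, whatever its size. A PHC effect that moves from survey to survey does not cancel, and it adds variance that the single-intercept model leaves out.

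The article's own description makes some movement plausible: a PHC is usually led by one doctor (Background, Workforce challenges), and the surveys span two years. The adjustment for time does not deal with it, because common survey effects remove only a trend shared by all PHCs.

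At stake are the confidence interval and type I error of the only primary outcome, and the meaning of the power claim. A reader is also likely to take the larger ICC as a safety margin against this kind of uncertainty.

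**Working it through.** **Inputs from the article:** 18 PHCs, six per step; five surveys, taken as months 0, 6, 12, 18 and 24, with the three groups treated at the last 3, 2 and 1 surveys; m = 150 per PHC per survey; 39% against 45%; two-sided 5%; ICC 0.03 planned, 0.01 observed.

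**Assumed:** p = 0.42 (midpoint) for the variance, and CAC, for which the article gives no value.

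**Formula.** On the proportion scale, with p(1−p) = 0.2436:

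- τ² = ICC × 0.2436
- s = (1−ICC) × 0.2436/m + (1−CAC)τ², the variance of one PHC-survey mean around its PHC level
- b = CAC × τ², the constant PHC part

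The Hussey-Hughes variance is

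Var = N·s(s + T·b) / [(N·U − W)s + (U² + N·T·U − T·W − N·V)b]

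with N = 18, T = 5, U = 36 treated PHC-surveys, W = 6² + 12² + 18² = 504 and V = 6(9 + 4 + 1) = 84. The two coefficients are 648 − 504 = 144 and 1296 + 3240 − 2520 − 1512 = 504. Power = Φ(0.06/SE − 1.96).

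**Step 1: the plan's figure.** ICC 0.03, CAC 1: s = 0.001575, b = 0.007308.
Var = 18 × 0.001575 × 0.03812 / (0.2268 + 3.6832) = 0.0002764; SE = 0.01663; power = Φ(3.609 − 1.960) = 95.0%.
So more than 90% reproduces. It is 92.9% at 135 per PHC (15% of about 300 per village, three villages), and 93.0% using only the four periods of Table 1. A t reference with 16 df, in place of the normal, gives 92.3% at 150 per PHC and five surveys.

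**Step 2: does the larger ICC protect?** ICC 0.01, CAC 1: s = 0.001608, b = 0.002436; SE = 0.01654; power 95.2%. Tripling the ICC moves power by 0.2 points.

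**Step 3: let PHC effects drift.** ICC 0.03, CAC 0.9: s = 0.001575 + 0.000731 = 0.002306, b = 0.006577.
Var = 18 × 0.002306 × 0.03519 / (0.3321 + 3.3149) = 0.0004005; SE = 0.0200; power = Φ(2.998 − 1.960) = 85.0%.

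**Step 4: a single-intercept analysis of the same data.** It still reports SE 0.0166 at ICC 0.03 (0.0165 at ICC 0.01). The true SE of its estimate comes from a sandwich calculation. Type I error = 2Φ(−1.96 × reported SE / true SE).

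| ICC | CAC | Power, correct model | True SE, single-intercept analysis | Its type I error |
|---|---|---|---|---|
| 0.03 | 1 | 95.0% | 0.0166 | 5.0% |
| 0.03 | 0.95 | 90.3% | 0.0184 | 7.7% |
| 0.03 | 0.9 | 85.0% | 0.0201 | 10.4% |
| 0.03 | 0.8 | 74.8% | 0.0230 | 15.6% |
| 0.01 | 1 | 95.2% | 0.0165 | 5.0% |
| 0.01 | 0.95 | 93.9% | 0.0171 | 5.8% |
| 0.01 | 0.9 | 92.5% | 0.0177 | 6.7% |
| 0.01 | 0.8 | 89.6% | 0.0187 | 8.3% |

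Simulation with 5,000 runs per setting gave type I errors of 8.0%, 10.1% and 16.0% at ICC 0.03, and 6.1%, 7.6% and 9.3% at ICC 0.01, for CAC 0.95, 0.9 and 0.8. With no drift it gave 4.5% to 5.3%.

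**Step 5: sensitivity.** At 135 per PHC and ICC 0.03, power is 87.8%, 82.5% and 72.5% at CAC 0.95, 0.9 and 0.8. If correlation instead decays exponentially with each six-month step, power at 150 per PHC is 82.5% at 0.9 and 70.9% at 0.8. Using the whole baseline census (about 900 per PHC) raises it only to 87.5% and 76.6% under the first drift structure. Power falls below 90% once CAC is under about 0.95 at ICC 0.03, but only under about 0.81 at ICC 0.01.

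The limits of this check are a linear approximation for a binary outcome, equal PHC sizes, and no village or person effects.

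**The case against.** **The article documents no drift.** This stands. A reader might infer that the planned standard errors are simply too small. The article does not support that: with CAC 1 they are right and the test keeps its level. A one-doctor PHC makes drift plausible but is not evidence of it.

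**The loss is mild at the ICC actually observed.** This also stands. At 0.01, power stays above 90% at CAC 0.9 and type I error is below 7%. CAC 0.8 at ICC 0.03 implies a PHC-by-survey component of 0.006 of the total variance, which is 60% of the whole observed ICC. That is a substantial drift. Even so, 0.03 is the planning value on which the article rests its claim, so the claim should be examined there too.

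**The article does not write out a single-intercept model.** This stands in part. It refers to methods based on Hussey and Hughes, does not name the power method, and an analysis plan not shown here may add terms. The single intercept is an inference from the model named, the one ICC, and the fact that the figure reproduces. The point here concerns the model named and the power stated, and is not a complaint about missing detail.

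**Repeat sampling and villages.** A reader might add that the follow-up samples come from one closed list, so that if drawn independently 1 − 0.85³ = 39% of follow-up observations come from people seen at another follow-up, and that villages are ignored. Neither makes the standard errors too small. Seeing the same people again adds positive correlation between a PHC's surveys, which sharpens within-PHC contrasts. With an assumed within-person correlation of 0.3 to 0.7, 135 per PHC, ICC 0.03 and no drift, the single-intercept type I error is 4.5% to 3.9%, slightly conservative. At CAC 0.9 the overlap lowers it to 9.3% to 8.6%. The same three villages per PHC are surveyed each time, so constant village effects largely cancel as well. There is no case here for drawing non-overlapping samples.

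**Conclusion.** The point holds as a conditional one. The power figure is not an arithmetic error, but it depends on an unstated assumption that no PHC drifts relative to the others over 24 months. The ICC of 0.03, presented as conservative, adds almost no margin under that assumption.

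If drift occurs, the damage depends on the ICC. Over CAC 0.95 to 0.8, power is 90% down to 75% at ICC 0.03 and 94% down to 90% at ICC 0.01. The type I error of a single-intercept analysis is about 8% to 16% and 6% to 8% respectively. The CAC range is assumed throughout.

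This is a recommended improvement. Reading it as a demonstrated flaw that invalidates the planned analysis would go beyond what the article shows.

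**What to change.** 1. Specify the primary model as categorical survey effects plus treatment, with random effects for PHC and for PHC-by-survey, or use an equivalent robust variance.
2. Use a small-sample reference suited to 18 PHCs, for example Kenward-Roger degrees of freedom or a permutation test that respects the stratified allocation.
3. Replace the single power figure with power over CAC 0.8 to 1.0 at both ICC 0.01 and ICC 0.03, and say that the larger ICC alone adds little protection.
4. State that time adjustment removes only change common to all PHCs.

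If the analysis plan already contains items 1 and 2, only the power statement and the remark on time adjustment need changing.

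The cost is wording, a somewhat wider confidence interval and a less favourable stated power. At 150 per PHC and with a normal reference, that power is about 75% to 95% at ICC 0.03 and 90% to 95% at ICC 0.01. The small-sample reference takes off a few points more (95.0% becomes 92.3% with no drift and 16 df). The design, sample and data collection do not change.

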### Economic and process evaluation

The economic evaluation will have a trial-based component and a modelled evaluation of long-term costs and outcomes. The intervention cost will be based on salaries, training, equipment and other costs incurred with implementation of the intervention. Trial-based data, however, cannot capture costs and outcomes beyond the trial. A decision-analytic model will enable long-term cardiovascular morbidity, quality of life and survival to be simulated. Cost-effectiveness will be calculated in terms of incremental cost per quality adjusted life years gained. This will better inform policy makers as to the resource consequences of rolling out this program to scale.

A detailed awareness of local contextual factors will be critical to understanding the impact of the intervention and any barriers to its implementation. The process evaluation will be informed by behaviour change theory [25], assessing how well the new system of service provision fits within the usual processes of current service provision in the villages and PHCs centres. A mixed methods approach to investigate why the intervention strategy may or may not have been effective and which intervention components were most influential will be used. Three data sources will be used: de-identified usage data from the tablet based system; patient and provider surveys; and semi-structured interviews with a purposive sample of participants and care providers toward the end of study.

### Ethical considerations

The study is approved by the Centre for Chronic Disease Control Institutional Ethics Committee (IEC), New Delhi and the University of Sydney Human Research Ethics Committee (HREC), NSW, Sydney. It is also registered in the Clinical Trials Registry of India. The study has also been discussed with each village Panchayat. Informed consent will be obtained from all participants contributing data before the randomisation process. All data collection and reporting will be compliant with national privacy law, and no report will allow an individual participant to be identified. Data will be securely stored at the George Institute Hyderabad. All study records and documents will be stored for a minimum of seven years from the end of the study or for a period as required by any individual HREC.

### Trial status

The study will be initiated with a household baseline survey in all 54 villages by the fourth quarter of 2013. Randomisation of PHCs and follow-up village surveys of high risk individuals will continue until the first quarter of 2016, followed by analysis and dissemination of the findings in middle of 2016.

## Discussion

SMARTHealth India focuses on a ‘real life’ implementation of a complex intervention. It represents a case study into ‘Integrated Innovation’ [26], incorporating a science/technology component (Smart Tablet, CDSS, and cutting edge trial design), a social component (innovative workforce strategies), and a business component (integration with existing health system infrastructure). Despite great promise for m-health interventions to improve access to effective healthcare, there remains considerable uncertainty about how this can be successfully achieved. These uncertainties pose substantial dilemmas for health system planners, particularly in LMICs. This project will rigorously explore the challenges of implementing well-established evidence into practice.

### Strengths and limitations

The strengths of the study are that it explores the challenges of implementing a complex intervention, taking into consideration policy, healthcare providers, and consumer perspectives. The evidence generated thus has substantial potential to inform decision-making for system planners on a scalable solution to increasing access to high quality primary healthcare for common chronic conditions.

The main limitation is that it is conducted in one rural region of one country, and the findings may not be generalizable to elsewhere. Integrating the intervention with the existing primary healthcare system, which is broadly similar in all parts of India, will help to mitigate this and enhance the relevance of the results across India and other regions with similar health system structures. Another potential limitation is that by using a stepped-wedge design, secular changes in the region during the study period may bias the outcomes. However, considering the study duration, time adjustment in the analysis, and recommendations by key stakeholders that access to the intervention be provided to all centres, this design provides, on balance, the most acceptable method to test the study hypothesis in a rigorous but pragmatic manner.

### Significance

The findings from this study are likely to advance locally relevant knowledge on scaling up a strategy to overcome entrenched inequities in access to effective healthcare for under-served populations. Such approaches, if found to be effective and cost-effective and combined with effective population-based strategies, have the potential to positively impact the healthcare of millions of Indians on a daily basis and will have wider applicability for other LMICs.

## Abbreviations

BP: Blood pressure; CVD: Cardiovascular diseases; PHC: Primary health centre; ASHA: Accredited social health activist; CDSS: Clinical decision support system; LMIC: Low and middle income countries; WHO/ISH: World health organisation/international society of hypertension; NPCDCS: National programme for cancer, diabetes, cardiovascular diseases and Stroke; cRCT: Cluster randomised controlled trial; IEC: Institutional ethics committee; HREC: Human research ethics committee.
